#### Statistical analyses

The primary endpoint and all continuous secondary endpoints will be analyzed using a linear mixed-effects model with period, sequence and procedure as fixed effects, and a patient nested within sequence as a random effect. For the response rate, a logistic mixed-effects model with the same specifications will be used. The response rate will be defined as a decrease in AHI of at least 50% compared to baseline or an AHI under treatment of < 15 events/h. Post-hoc comparisons will be made based on these models, correcting for multiple testing by means of Bonferroni–Holm stepdown correction.

Non-inferiority of PSG compared to DISE will be judged based on the confidence intervals obtained from the mixed-effects models. When the lower limit of the confidence interval falls above the predefined non-inferiority margin, non-inferiority will be concluded. The non-inferiority margin for the percent change in AHI from baseline will be set at 10%. For the change in VAS for snoring, the ESS, the CIS20R and its fatigue subscale the margin is considered, respectively, to be 1, 2, 5 and 10 points. Additionally, differences between subjective titration and both RCMP titration protocols will be investigated for all of the secondary endpoints.

If more than 20% of all information regarding one endpoint is missing, a sensitivity analysis will be conducted for this endpoint using multiple imputation. Results of the original analysis will be interpreted in the light of these sensitivity analyses.

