### Statistics

#### Sample size calculation

The primary endpoint of this study protocol is to assess equivalence of the protrusive position obtained with the three titration protocols. We need 65 patients to have 80% power to show equivalence of two procedures with an equivalence margin of 1.6 and a standard deviation of 3.7. These numbers are based on the results of Civelek et al. [12]. The significance level of 0.05 will be Bonferroni corrected to 0.0167, to account for comparing three titration protocols.

For every patient dropping out of the study before the first visit, an extra patient will be recruited. Based on previous studies, the dropout rate is anticipated to be around 20%, so we expect to include 78 patients in total.

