#### Randomization

This study design will lead to six different sequences of titration procedures (Table 1). The patients will be randomly allocated to one of the six possible sequences of titration procedures. To ensure that the groups are of approximately the same size, block randomization will be used. The allocation sequence will be automatically generated and will be stratified by OSA severity (moderate/severe), gender and body mass index (BMI < 26 kg/m^2^; 26 ≤ BMI < 30 kg/m^2^; 30 kg/m^2^ ≤ BMI).

**Table 1 Tab1:** Overview of the six possible titration sequences in this study protocol

Sequence	Order of titration procedures		
1	Subjective titration	RCMP titration during PSG	RCMP titration during DISE
2	Subjective titration	RCMP titration during DISE	RCMP titration during PSG
3	RCMP titration during PSG	Subjective titration	RCMP titration during DISE
4	RCMP titration during PSG	RCMP titration during DISE	Subjective titration
5	RCMP titration during DISE	Subjective titration	RCMP titration during PSG
6	RCMP titration during DISE	RCMP titration during PSG	Subjective titration

*DISE* drug-induced sleep endoscopy, *PSG* type 1 polysomnography, *RCMP* remotely controlled mandibular positioner

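### The primary endpoint is sized as an equivalence test, but no equivalence decision rule is carried into its analysis, and the two sections use different multiplicity rules

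*Protocol article*

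**What the plan says.** The Sample size calculation section of the protocol article sets the objective: "The primary endpoint of this study protocol is to assess equivalence of the protrusive position obtained with the three titration protocols". The size follows from it: "We need 65 patients to have 80% power to show equivalence of two procedures". The margin is 1.6 and the SD 3.7, with no unit given for either. Multiplicity is handled by a fixed split: "The significance level of 0.05 will be Bonferroni corrected to 0.0167, to account for comparing three titration protocols".

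The Statistical analyses section puts the primary endpoint and all continuous secondary endpoints through the same linear mixed model (period, sequence and procedure fixed; patient within sequence random). It then states: "Post-hoc comparisons will be made based on these models, correcting for multiple testing by means of" a Bonferroni-Holm step-down procedure. Neither equivalence nor the 1.6 margin appears there.

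The same section does contain one rule that compares a confidence limit with a margin. It is one-sided, compares PSG-guided with DISE-assisted titration, and has margins for percent change in AHI, snoring VAS, ESS and the CIS20R. The Secondary outcomes section ties that rule to the secondary outcomes. The Primary outcome section says only that positions will be assessed and compared between methods.

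**The concern.** The sizing and the analysis of the primary endpoint do not describe the same test. An equivalence claim needs the interval for the difference to be compared with a margin on both sides. Pairwise comparisons from a mixed model, with a multiplicity correction and no margin, are ordinarily tests of a zero difference. Such a test can show that two procedures differ, but failing to reject shows nothing about whether they agree within 1.6.

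A condensed article may leave detail to an analysis plan. Here, however, the section spells out margins and an interval rule for the secondary outcomes and leaves the primary endpoint, which determined the sample size, with comparisons that do not test its hypothesis.

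The interval level is also open. A fixed 0.0167 implies one particular interval, whereas Holm uses different levels at successive steps and so implies no single one. Nor is it clear whether the claim is about each pair or about all three together: the objective names three procedures, but the power statement covers two. What is at stake is the error rate of the trial's main conclusion.

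**Working it through.** **Inputs** (all from Sample size calculation): n = 65, power 80%, margin 1.6, SD 3.7, alpha 0.05/3 = 0.0167. **Assumptions:** 3.7 is the SD of the within-patient difference, and 0.0167 applies to each one-sided test. The article states neither, but together they reproduce its figure.

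**1. Reproduce the 65.** Two one-sided paired tests (TOST), true difference 0.
- Normal approximation: n = [SD × (z(1 − 0.0167) + z(0.90)) / margin]² = [3.7 × (2.127 + 1.282) / 1.6]² = 62.1, so 63.
- Exact paired-t calculation: the smallest n with power of at least 0.80 is 65, with power 0.805.
- Other one-sided levels do not give 65: 0.05 gives 48, 0.025 gives 59 and 0.0083 gives 76.

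The sizing is therefore a genuine equivalence calculation at one-sided 0.0167. The matching interval has level 1 − 2 × 0.0167 = 96.7%.

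**2. Error of the planned test at the margin.** With a true difference of 1.6, the TOST at n = 65 declares equivalence in 1.67% of trials.

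**3. What a difference test does at the same point.**
- Standard error = 3.7/√65 = 0.459.
- Noncentrality = 1.6/0.459 = 3.49, with 64 degrees of freedom.
- P(non-significant) = P(|T| < critical value), where T is noncentral t.

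| Two-sided alpha | Critical t | P(non-significant), true difference 1.6 |
|---|---|---|
| 0.0167 | 2.458 | 15.5% |
| 0.025 | 2.295 | 12.0% |
| 0.05 | 1.998 | 7.0% |

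The three rows are the successive Holm levels for three comparisons. At 0.0167 the ratio to the planned error is 15.5/1.67, about nine.

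**4. Fewer evaluable patients.** At two-sided 0.0167 the non-significance rate rises to 17.6% with 62 patients (78 × 0.8, rounded) and 26.2% with 52 (65 × 0.8). The TOST stays at or below 1.67%. A difference test thus becomes more lenient as information is lost, whereas an equivalence test does not.

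**5. Power under the rules that could be written.** Simulation at n = 65 with equal variances, zero true differences and pooled error.
- All three pairs required to pass, one-sided 0.05 each (90% intervals): joint power about 0.84.
- All three pairs passing under Holm applied to TOST p-values: about 0.82.
- One pair at 0.0167: about 0.80, as in step 1.

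**The case against.** The strongest reply is that the sizing section already publishes the equivalence aim, the margin and the alpha. The analysis sentence does not call the comparisons difference tests, and a mixed model is fully compatible with equivalence testing because its intervals can be compared with ±1.6. Read together, the sections could mean equivalence comparisons from the model. That is a fair account of what the planners probably had in mind, and step 1 supports it. But the link is not written, and the one margin rule in the analysis section is for other endpoints, so the primary analysis as worded does not test the primary hypothesis.

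Three stronger readings are tempting, and the article does not support them:
- **That equivalence will be read from non-significance.** This is nowhere stated. The 15.5% and 7.0% show what that reading would cost; they are not the planned error rate.
- **That Holm is wrong here.** Holm can be applied to TOST p-values and is never less powerful than plain Bonferroni. Sizing on Bonferroni and analysing with Holm is conservative. What remains is that one rule, and the interval that goes with it, should be named.
- **That the trial is underpowered for an all-three claim.** The figure behind this, about 0.62, comes from applying a fixed 0.0167 to every pair. Under the stated Holm rule, all-three power is about 0.82, and the article promises power only for two procedures.

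It also stands that 15.5% applies only at the strictest Holm step.

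**Conclusion.** The point holds in this form, and the plan is wrong as written. The primary endpoint is sized as a two-sided equivalence test at one-sided 0.0167 per test, but its analysis section contains no equivalence rule, no margin and no interval level for it. Comparisons read as difference tests cannot establish equivalence. At n = 65 and a true difference at the margin, non-significance occurs in 15.5% of trials at two-sided 0.0167 and 7.0% at 0.05, against 1.67% for the test that was sized. The fixed Bonferroni level and Holm also need to be reconciled, and the intended claim stated.

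The figures rest on 3.7 being the SD of the paired difference and on a paired-t analysis standing in for the mixed model. The first assumption reproduces the stated 65. The conclusion that the rule is missing depends on neither. Neither the mixed model nor the sample size for pairwise claims is at fault.

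**What to change.** In Statistical analyses, state for the primary endpoint that two procedures are concluded equivalent only if the mixed-model confidence interval for their difference lies wholly within -1.6 to +1.6, and give the unit. Then state the claim and use one multiplicity rule to match:
- **Separate pairwise claims:** either 96.7% intervals (one-sided 0.0167, as sized; power about 0.80 at n = 65) or Holm applied to the TOST p-values.
- **A claim that all three are equivalent:** 90% intervals with all three pairs required to pass (joint power about 0.84 at n = 65). No alpha split is needed, because every pair must succeed.

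Make the multiplicity sentence in Sample size calculation agree with the choice. The cost is protocol wording only: no new data, no design change, and the 65 evaluable patients stand. It should be settled before any comparative results are seen, because it decides the primary conclusion.

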#### Secondary outcomes

Efficacy of the MAD therapy will be assessed as a measure of treatment outcome by comparing the baseline AHI with the AHI under MAD therapy.

In addition, structured questionnaires to evaluate tolerance and side effects, subjective snoring, daytime sleepiness and fatigue will be completed by all patients at baseline and at follow-up evaluations.

The degree of daytime sleepiness will be assessed using the Epworth Sleepiness Scale (ESS) [37]. A standard 10-point visual analog scale (VAS) for the scoring of snoring as assessed by the bed partner will be used only in patients who have a bed partner who is able to report the snoring intensity. This VAS is ranging from 0 to 10, with 0 equaling no snoring and 10 causing the bed partner to leave the room or sleep separately [38]. Heavy snoring will be defined as a VAS snoring index of at least 7. Fatigue severity will be measured by the Checklist Individual Strength (CIS20R) [36]. The CIS20R, and more specifically its subscale on fatigue, is a standardized and validated questionnaire that consists of eight items scored on a 7-point Likert scale. The scores range from 8 (normal fatigue) to 56 (most severe fatigue). A score of 26 or lower indicates a normal energy level, scores between 27 and 35 indicate mild fatigue and a score of 36 or higher indicates severe fatigue.

For all secondary outcomes, non-inferiority of RCMP titration with PSG compared to RCMP titration with DISE will be assessed. Additionally, differences between subjective titration and both RCMP titration protocols will be investigated.

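### Holm is valid for the post-hoc comparisons, but if the family is all three pairwise difference tests it is needlessly conservative; naming the family, or a restricted step-down, removes the loss at no cost

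*Protocol article*

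**What the plan says.** Under Statistical analyses, the primary endpoint and the continuous secondary endpoints are analysed with linear mixed models that include procedure as a three-level fixed effect; the response rate gets a logistic counterpart. The adjustment is fixed in one sentence: "Post-hoc comparisons will be made based on these models, correcting for multiple testing by means of Bonferroni–Holm stepdown correction". The number of tests in the family is not given.

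Three places bear on what the family might be:

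- Sample size calculation: "The significance level of 0.05 will be Bonferroni corrected to 0.0167, to account for comparing three titration protocols". This concerns the primary equivalence objective.
- Secondary outcomes: "Additionally, differences between subjective titration and both RCMP titration protocols will be investigated". Statistical analyses repeats this for all secondary endpoints. It names two difference comparisons.
- Statistical analyses: PSG versus DISE on the secondary endpoints is judged by a non-inferiority confidence interval, not by a difference test.

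**The concern.** Post-hoc comparison of a three-level factor ordinarily yields three pairs. Holm then tests the ordered p-values at 0.05/3 = 0.0167, 0.05/2 = 0.025 and 0.05. Holm is built for hypotheses that can be true or false in any combination, and three pairwise equalities cannot. If one pair differs, the other two equalities cannot both hold, because together they would make the first pair equal.

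The comparison that pays is typically the second of the two between subjective titration and an RCMP method: it is held at 0.025 where 0.05 would be valid. At stake is which differences can be declared on AHI, response and symptoms, not whether any false-positive rate is exceeded.

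**Working it through.** **1. The plan's own figure.** Inputs from Sample size calculation: margin 1.6, SD 3.7, per-comparison level 0.0167. The stated result is "We need 65 patients to have 80% power to show equivalence of two procedures". Take 3.7 as the SD of within-patient differences, a true difference of 0, and two one-sided tests at 0.0167. The normal approximation is n = ((z(0.9833) + z(0.90)) × 3.7/1.6)² = ((2.13 + 1.28) × 2.3125)² ≈ 62.2, that is 63. The exact t version gives 65, with power 80.5%. The stated 65 reproduces, so 3.7 is usable as a paired SD below.

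**2. Thresholds under each family.**

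| Procedure | Step 1 | Step 2 | Step 3 |
|---|---|---|---|
| Holm, three pairs | 0.0167 | 0.025 | 0.05 |
| Restricted step-down (Shaffer), three pairs | 0.0167 | 0.05 | 0.05 |
| Holm, two named tests | 0.025 | 0.05 | – |

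Step 1 is the same for the first two rows and the later thresholds are never smaller, so the restricted procedure rejects everything that three-test Holm rejects.

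**3. Error control (simulated).** With all three procedures equal, familywise error is 4.3% for both three-pair procedures. With only PSG = DISE true and subjective far away, it is 5.0% for both.

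**4. Power to show both subjective-versus-RCMP differences.** Assumptions: 65 patients, PSG = DISE, SD of differences 3.7, correlation 0.5 between the two contrasts, 200,000 runs per case. The documents give no expected difference between subjective titration and the RCMP methods, so a range is shown. Gains are from unrounded values.

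| True difference (in SDs) | Single unadjusted test | Holm, three | Restricted, three | Gain (points) | Holm, two |
|---|---|---|---|---|---|
| 0.5 (0.14) | 19.1% | 4.2% | 6.5% | 2.3 | 7.4% |
| 0.8 (0.22) | 41.0% | 16.0% | 22.0% | 6.0 | 23.6% |
| 1.0 (0.27) | 58.1% | 29.9% | 38.2% | 8.3 | 40.3% |
| 1.2 (0.32) | 73.9% | 48.0% | 57.4% | 9.3 | 59.2% |
| 1.3 (0.35) | 80.3% | 57.3% | 66.5% | 9.1 | 68.1% |
| 1.5 (0.41) | 90.1% | 74.5% | 81.6% | 7.1 | 82.7% |
| 1.6 (0.43) | 93.3% | 81.5% | 87.3% | 5.8 | 88.1% |
| 2.0 (0.54) | 99.1% | 96.7% | 98.1% | 1.5 | 98.3% |

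**5. Sensitivity.**

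- Number analysed: the article says "the dropout rate is anticipated to be around 20%, so we expect to include 78 patients in total", and 78 × 0.8 ≈ 62. At a difference of 1.6 the gain is 6.3 points with 62 completers and 3.8 with 78.
- Standardised shifts with 62 completers (error df 120, 400,000 runs): at about 70%, 80% and 90% single-test power, three-test Holm gives 43.0%, 56.0% and 73.4%, and the restricted step-down 52.2%, 65.0% and 80.7%. The gains are 9.2, 9.0 and 7.3 points.
- Unequal true differences with 65 patients: 1.6 and 1.0 gives 8.9 points, 2.0 and 1.0 gives 5.9, and 2.5 and 1.2 gives 1.9.
- Showing at least one subjective-versus-RCMP difference changes by 0.3 points or less.

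**6. If the family is the two named tests.** Holm already tests at 0.025 and then 0.05, so no power is lost. In the 62-completer setting it shows both differences in 54.2%, 66.7% and 81.9% of runs, which is 1 to 2 points above the restricted three-pair procedure. For at least one difference it gives 75.2%, 84.2% and 93.1%, against 69.4%, 79.7% and 90.5%.

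**The case against.** The strongest reply is that the three-test family is inferred. The secondary endpoints name two difference tests and leave PSG versus DISE to a non-inferiority interval. The phrase "to account for comparing three titration protocols" belongs to the primary equivalence objective. On the two-test reading Holm is already efficient, and imposing the three-pair step-down would cost power (step 6). This stands, and it is why the remedy has to depend on the family. It does not remove the point: the sentence on post-hoc comparisons follows from a three-level model and also permits the all-pairs reading, which does lose power.

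It can also be said that Holm is standard, prespecified and valid, and that the composition of the family is commonly left to an analysis plan that is not shown. That stands too, so nothing here is an error or an omission.

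A reader might infer three stronger things that the documents do not support:

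- That a fixed 7 to 9 points is lost. The size depends on an effect that the article does not give.
- That showing both differences is a success criterion. The article says only that these differences will be investigated; it sets no joint claim and no power target for them.
- That the same shortcut serves the primary equivalence tests. It does not. There each null says that a difference is at least 1.6. Two methods can coincide while the third lies more than 1.6 from both, so after one rejection two nulls can still be true.

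**Conclusion.** The point holds as an optional efficiency gain and not as a fault in the plan. If all three pairs are tested for difference on an endpoint, replacing Holm by the restricted step-down keeps every Holm rejection and the 5% familywise error. It raises the chance of showing both subjective-versus-RCMP differences by up to about 9 points when PSG = DISE and single-test power is about 70–90%. With the primary endpoint's 1.6 and 3.7 borrowed and 65 patients, the gain is 5.8 points. It shrinks for small, very large or some unequal effects. If only the two named comparisons form the family, the gain is zero and Holm should stay.

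The logical argument needs only valid p-values, so it also covers the response rate. The simulated sizes assume continuous outcomes with a common within-patient variance.

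**What to change.** In Statistical analyses, state the family for difference tests on each endpoint and choose one of two options:

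- (a) Limit the family to subjective versus PSG-guided and subjective versus DISE-assisted titration, with Holm at 0.025 and then 0.05. Leave PSG versus DISE to its non-inferiority interval.
- (b) If all three pairs are to be tested for difference, replace Holm by Shaffer's restricted step-down: the smallest p-value at 0.05/3 and, if it is rejected, the other two each at 0.05.

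Option (a) matches the comparisons that the article names and gives slightly more power for them, but it forgoes a difference test of PSG versus DISE. A global test at 0.05 followed by each pair at 0.05 is not a strict replacement for Holm, because it missed a Holm rejection in up to 0.4% of simulated runs.

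Leave the primary equivalence tests as they are. The cost is one sentence in the plan, settled before the comparative data are seen, and one line of code. It needs no additional patients and gives up no error control.

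### The non-inferiority margin for the CIS20R fatigue subscale (10 points) is twice that for the whole CIS20R (5 points), and wider than the protocol's mild-fatigue band

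*Protocol article*

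**What the plan says.** The Statistical analyses section of the protocol article sets non-inferiority margins for PSG-guided against DISE-assisted titration. After a 10% margin for the percent change in AHI, it names four questionnaire outcomes in order: snoring VAS, ESS, CIS20R, and the CIS20R fatigue subscale. The sentence ends: "the CIS20R and its fatigue subscale the margin is considered, respectively, to be 1, 2, 5 and 10 points". The assignment is therefore VAS 1, ESS 2, whole CIS20R 5 and fatigue subscale 10. No reason is given for any of these values.

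The decision rule in the same section is "When the lower limit of the confidence interval falls above the predefined non-inferiority margin, non-inferiority will be concluded".

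The scale is described under Secondary outcomes, in a sentence that begins "The CIS20R, and more specifically its subscale on fatigue". The description "consists of eight items scored on a 7-point Likert scale" follows, with scores running from 8 to 56. The cut-offs are 26 or lower for a normal energy level, and then "scores between 27 and 35 indicate mild fatigue and a score of 36 or higher indicates severe fatigue". The item count and range of the whole CIS20R are not stated.

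**The concern.** A subscale cannot have a wider range than the scale that contains it. One would expect the margin for the part to be no larger than the margin for the whole, yet here it is double. The larger value also falls on the score that measures fatigue most directly, and it is wide against the severity bands that the protocol prints for that score.

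The margin is the threshold that decides the conclusion. If 10 was not meant for the subscale, PSG-guided titration could be declared non-inferior on fatigue with a mean loss that the intended margin would have ruled out. A correction made after the results are known would look data-driven.

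**Working it through.** **Plan's own figures.** The margins 5 and 10 are stated without derivation, so there is nothing to reproduce. The one computed figure in the Statistics section is N = 65. As a paired two one-sided tests calculation with true difference 0, SD 3.7, margin 1.6 and α = 0.0167 per test, the normal approximation is (3.7 × (2.13 + 1.28) / 1.6)² ≈ 62.1, so 63. The exact t calculation gives 65, with power 80.5%. N = 65 reproduces and does not use the CIS20R margins.

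**Inputs** (Secondary outcomes and Statistical analyses)
- Fatigue subscale: 8 items, range 8 to 56; normal ≤ 26, mild 27 to 35, severe ≥ 36; margin 10.
- Whole CIS20R: range not stated; margin 5.
- Snoring VAS: range 0 to 10; margin 1.

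**Margin as a share of range**
- Subscale: 10 / (56 − 8) = 10/48 = 20.8%, or 10/8 = 1.25 points per item.
- Snoring VAS: 1/10 = 10%.
- Whole CIS20R: its range is at least that of its subscale, so the share is at most 5/48 = 10.4%. If it has 20 items scored 1 to 7 (an assumption from the name), the range is 6 × 20 = 120 and the share is 5/120 = 4.2%. Assumed counts of 12, 16 and 24 items give 6.9%, 5.2% and 3.5%.
- In relative terms the subscale margin is therefore at least twice that of the whole, and five times with 20 items. The factor of two needs no assumed item count.

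**Margin against the severity bands**
- The mild band holds 35 − 27 + 1 = 9 scores, and 10 exceeds 9.
- 26 + 10 = 36: from the top of normal to the severe threshold.
- 27 + 9 = 36: a shift still inside the margin takes the lowest mild score into the severe class.

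**Agreement between the two tests.** If the total sums its items (assumed), a true worsening of 6 to 9 points confined to the fatigue items would exceed the total-score margin and stay inside the subscale margin.

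**What the rule would let through.** The document gives no SD for fatigue differences and no confidence level for these tests. Assume 65 complete pairs, a two-sided 95% interval and a simple paired comparison. The half-width is then t × SD/√65, with t ≈ 2.00 and √65 ≈ 8.06. The largest observed mean loss that still passes is the margin minus the half-width.

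| Assumed SD of paired differences | Half-width | Passes with margin 10 if loss is below | Passes with margin 5 if loss is below |
|---|---|---|---|
| 8 | 2.0 | 8.0 | 3.0 |
| 10 | 2.5 | 7.5 | 2.5 |
| 12 | 3.0 | 7.0 | 2.0 |

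Whichever SD is assumed, there is a 5-point window of observed mean loss in which the two margins give opposite conclusions.

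**If the values are swapped.** The subscale margin becomes 5/48 = 10.4% of range, close to the VAS figure and narrower than the mild band. The whole-scale margin becomes 10/120 = 8.3% under the 20-item assumption.

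**The case against.** Four objections have force.

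- **Individual bands against a mean margin.** The cut-offs classify patients, while the margin applies to a mean difference between procedures. A patient who goes from 15 to 25 stays normal, and one who goes from 20 to 30 becomes mild. Only a patient near a cut-off makes the full jump. This stands: the band width gives context for judging 10 points, and is not in itself a test of error.
- **The confidence-limit rule.** A reader might infer that non-inferiority could readily be declared with patients on average a full severity class worse. The rule does not support that, because the limit and not the estimate must clear the margin. For an observed mean loss of 9 points to pass with 65 pairs, the half-width must be below 1. That needs an SD of paired differences below about 8.06/2.00 = 4.0 (95% interval) or 8.06/1.67 = 4.8 (90%). It is an edge case. A loss of about 7 to 8 points could pass under the SDs assumed above, and that is still substantial.
- **Transposition is not proven.** A reader might take the swap as certain. Neither value is derived, so the document cannot separate a swap from a poorly chosen number. The closeness of the swapped values to the VAS margin is suggestive, but nothing in the protocol says that margins should be a constant share of range.
- **The total-score margin.** A 5-point margin on the whole scale is strict, and strictness makes a false claim of non-inferiority harder. It is not an error on its own.

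One could also read Secondary outcomes loosely, as describing the whole CIS20R as the eight-item scale. That does not rescue the sentence, since one scale would then carry two different margins.

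**Conclusion.** The pair of margins is incoherent as written. The part is allowed twice the deterioration of the whole: 20.8% of the subscale's range, against at most 10.4% for the whole scale. The subscale margin also exceeds the mild band. These results rest only on the document's own range, cut-offs and ordering. The 4.2% and 8.3% figures rest on an assumed 20 items, and the passing losses on assumed SDs and a 95% interval.

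A transposition is a likely explanation and remains unproven. Nor does the document support a general rule that the subscale margin must lie below nine points. It supports only the demand that a margin wider than the mild band be explained.

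Severity is moderate. The conclusion for a secondary endpoint depends on the value. The primary endpoint (protrusive position), N = 65 and the AHI margin are untouched.

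**What to change.** Before analysis, the sponsor should confirm which value belongs to which score and correct the sentence under Statistical analyses.

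- If the two were transposed, state 10 points for the CIS20R total and 5 for the fatigue subscale.
- If 10 points was intended for the subscale, justify it against the cut-offs under Secondary outcomes, or reduce it. Also explain why the part has a wider margin than the whole.

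The change is one line of text. If the subscale margin falls, one secondary endpoint faces a stricter test and non-inferiority on fatigue becomes harder to show. The sample size and primary analysis need no change.
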